### Analysis plan

Randomization results will be compared with a preplanned randomization schedule to ensure randomization integrity. To verify comparability of the randomized groups, baseline characteristics (age, sex, race, and education level) will be compared between randomized groups for veterans and caregivers separately as well as veterans’ comorbid medical conditions, the Charlson comorbidity index, number of primary care visits, and acute care use during the year prior to enrollment. This analysis will be conducted using analysis of covariance models for continuous variables and the Cochran-Mantel-Hansel statistic for categorical variables while controlling for the stratification variable of primary diagnosis (ADRD or TBI). The distributions of continuous variables will be examined, and transformation or nonparametric methods will be used in cases of violation to the normal distribution assumption. In addition, the frequency distribution will be examined for all categorical variables, and exact inference procedures will be used in cases of zero or small cell size. All analyses will be conducted with SAS 9.4 software (SAS Institute, Cary, NC, USA).

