Mixed effects models will be used with longitudinally collected QoL scores from veterans as the dependent variable, and randomization group, time, and interaction between group and time as the independent variables while adjusting for the stratification variable of primary diagnosis (ADRD or TBI) and baseline variables that are found to be different between the two groups. An unstructured variance–covariance matrix will be used in the mixed effects model to adjust for potential correlations among measures obtained from the same individual over time. A significant interaction between group and time would indicate differences in QoL changes over time between the ABC ANSWER and control groups. Linear contrasts will be used to compare the QoL scores at each follow-up time between the two groups. Absent significant interaction, significant main group effects would suggest differences in QoL measures between the two groups across all follow-up times. Parametric estimation and inference procedures for the mixed effects models are conducted using the maximum likelihood approach with robust parametric estimation and inference under many missing data mechanisms [68]. In addition, other covariates will be included in the mixed effects models to determine whether specific family member characteristics (e.g., relationship to veteran, frequency or types of contact, other people living in the household) are associated with QoL changes over time. Similar analysis will be conducted for the outcome of caregiver QoL.

Additionally, a mixed effects model will be conducted with caregiver QoL as the outcome variable and veterans’ QoL measures as an additional independent variable to determine how much of the intervention effect on caregiver QoL is mediated through changes in veterans’ QoL measures. By realigning veteran QoL and caregiver QoL, we can also determine whether any mediation effect from veteran QoL is concurrent or has lagged in time.

Similar linear mixed models will be fit for outcomes of caregiver burden (OCBS) and outcomes collected on both veteran and caregiver: depression (CES-D), anxiety (GAD-7), and dyadic strain (dyadic relationship strain and role captivity). All veteran and caregiver outcomes will be fit with separate models. Linear contrasts obtained from the models will be the differences in mean score between the intervention group and the control group at each follow-up time.

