For dyad analyses, we will use the dyadic nature of the study design and assess how caregivers’ outcomes are related to veterans’ measures. We will first explore the degree of concordance between paired veteran–caregiver reports using mixed effects models with concurrent veterans’ measures from the same time points as measures of caregivers. ICCs between veteran and caregiver measures will be calculated to assess the degree of chance-corrected agreement between individual veteran and caregiver outcomes, controlling for within-person correlations over time. Mixed effects models will also be used to explore potential mediation effect of the intervention on caregivers’ outcomes from the effect on veterans’ outcomes. For example, we will examine whether intervention effect on caregiver QoL, burden score, and depressive or anxiety symptoms is mediated by an increase in veterans’ QoL or decreased depressive or anxiety symptoms in the intervention group versus the control group. No interim analyses are planned.

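### The veteran-QoL mediation analysis states no adjustment for mediator–outcome confounders and could report a mediated share where there is none

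*Protocol article*

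**What the plan says.** All of this is in the Analysis plan section of the protocol article.

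- **Method and reading.** Veteran QoL enters the caregiver QoL mixed model as one more predictor. The stated aim is "to determine how much of the intervention effect on caregiver QoL is mediated through changes in" the veteran's own scores. The article adds that by realigning the two series "we can also determine whether any mediation effect from veteran QoL is concurrent or has lagged in time".
- **Covariates of the base model.** Group, time and their interaction, "adjusting for the stratification variable of primary diagnosis (ADRD or TBI) and baseline variables that are found to be different between the two groups".
- **Variables screened for imbalance.** "baseline characteristics (age, sex, race, and education level) will be compared between randomized groups", plus veterans' comorbid conditions, the Charlson index, primary care visits and acute care use. Baseline QoL is not in that list.
- **Family characteristics.** The article says that "other covariates will be included in the mixed effects models to determine whether specific family member characteristics" are associated with QoL change over time. Confounding is not given as the reason.
- **Dyad analyses.** A later paragraph begins "We will first explore the degree of concordance between paired" veteran and caregiver reports. It then describes the mediation work as exploratory and extends it to caregiver burden, depression and anxiety.

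**The concern.** Randomisation protects the comparison of arms. It does not protect the relation between veteran QoL and caregiver QoL within an arm. Two people in one household can be moved by the same things, and the QOL-AD, used for both, covers interpersonal relationships and finances. If such shared causes are left uncontrolled, the coefficient on veteran QoL picks them up. Concurrent scores also cannot tell veteran-to-caregiver influence from the reverse.

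The covariate rule does not help. A variable that is perfectly balanced between arms can still drive both members' QoL, and a rule based on imbalance would leave it out.

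At stake is the mechanism claim. The report could attribute part of the caregiver benefit to veteran improvement when none of it arose that way, and would understate the direct effect by the same amount. The same risk carries over to the other outcomes named for mediation.

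**Working it through.** **The plan's own figure.** The article gives no figure for the mediation analysis. Its only related figure is power above 80% with 180 dyads (Statistical power section). A group effect averaged over the three follow-ups and adjusted for baseline reproduces this: 82.0% in the sustained scenario and 96.7% in the gradual one. Other variants differ (76.6% in the sustained scenario without baseline adjustment). Nothing below depends on this power.

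**Inputs from the Statistical power section.** Effects of 0.3 SD at 3, 6 and 12 months, or 0.17, 0.34 and 0.68 SD; within-person correlations of 0.4 (adjacent) and 0.2 (farther apart); 180 dyads.

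**Assumptions, not in the article.**
- r, the veteran–caregiver correlation from uncontrolled shared causes: 0 to 0.5.
- a/c: 1, with a range of 0.5 to 2.
- True mediation: zero.

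**Formula.** In SD units, let veteran QoL be M = aG + u and caregiver QoL be Y = cG + v, with corr(u, v) = r and no path from M to Y. Regressing Y on G and M gives:

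- coefficient on M: b = r
- direct effect: c − ra
- apparent mediated share: [c − (c − ra)]/c = r × a/c

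Example: r = 0.3 and a = c = 0.3 give a direct effect of 0.3 − 0.09 = 0.21 and a share of 0.09/0.3 = 30%, where the truth is 0%. Halving or doubling a/c gives 15% or 60%.

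**Mixed model with unstructured covariance, a/c = 1.** The size depends on how the shared influences behave over time. Shares without, then with, adjustment for both members' baseline QoL:

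| Shared influences | r = 0.1 | r = 0.2 | r = 0.3 | r = 0.5 |
|---|---|---|---|---|
| Same time pattern as the outcomes | 10% → 10% | 20% → 20% | 30% → 30% | 50% → 50% |
| Purely stable | 5% → 4% | 11% → 8% | 19% → 15% | not computed |
| Purely visit-specific | 13% → 14% | 26.5% → 28.5% | 42% → 45% | not computed |

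Simulation (1,000 trials of 180 dyads per setting, first pattern, r = 0.3) agrees. The 12-month total and direct effects were 0.295 and 0.204 in the sustained scenario (share about 31%), and 0.687 and 0.483 in the gradual one (about 30%). Both the 12-month veteran effect and b were significant in 54% and over 99% of trials, against about 4% and 5% at r = 0.

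**Lagged model (6-month veteran QoL, 12-month caregiver QoL, both baselines).** The coefficient is the first element of S⁻¹s. Here S is the correlation matrix of 6-month veteran, baseline veteran and baseline caregiver QoL, and s holds their correlations with 12-month caregiver QoL.

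- Shared influences at least partly visit-specific: a false share of about 7–20% for r = 0.2–0.5.
- Purely stable cause: S has off-diagonals 0.2, r, r and s = (r, r, 0.2), so b = 0.8r/(1.2 − 2r²). At r = 0.2 this is 0.16/1.12 = 14%; at r = 0.3 it is 0.24/1.02 = 24%.

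These shares take the 6-month veteran effect as equal to the 12-month caregiver effect. Lagging therefore helps in most patterns but never removes the bias. With a purely stable cause it does no better than the concurrent mixed model (11% and 19%).

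**When there is no bias.** At r = 0 the share is about zero. If the intervention does not change veteran QoL (a = 0), the expected indirect effect is zero whatever r is.

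**The case against.** The case against is substantial, and much of it limits the point.

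- **The model is not bare.** A reader might infer that there is no baseline or confounder adjustment at all. The text does not support that. Veteran QoL is added to a model that carries diagnosis, imbalanced baseline variables and possibly family characteristics. What is absent is a stated adjustment chosen for mediator–outcome confounding.
- **Baseline QoL may be present.** The model uses longitudinally collected scores, and the article does not say whether baseline is one of the repeated responses. Its absence cannot be asserted, and the table shows that adding it as a covariate changes little.
- **r and a/c are not in the article.** A reader might conclude that the trial would report a substantial false share. It could; the share runs from 0% upwards with r. Planning to measure concordance does not show that the authors expect shared causes.
- **The work is partly exploratory, and a lag is foreseen.** Both are true. No stated hypothesis concerns mediation.
- **Confounder lists and sensitivity analyses usually sit in a SAP.** Their absence from an article would be no finding on its own. What remains is what the article does fix: a method, a covariate rule with the wrong criterion, and a quantitative causal reading stronger than its own exploratory wording a paragraph later.

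**Conclusion.** The point holds in a limited form. The article reads the coefficient on a non-randomised, post-randomisation variable as the mediated share, with no stated control of mediator–outcome confounders. With zero true mediation, the concurrent model could show a share of about r × a/c: 0%, 10%, 30% and 50% at r = 0, 0.1, 0.3 and 0.5 when a/c = 1, and about 5–19% for r = 0.1–0.3 with a purely stable common cause.

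This rests on two conditions that the article does not quantify: uncontrolled shared causes within dyads, and an effect on veteran QoL. The article does hypothesise the second.

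A reader might also infer that the trial's main result is at risk. It is not: the between-group comparisons, including the primary one, do not use the mediator.

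**What to change.** 1. Make the time-ordered model that the article already foresees (earlier veteran QoL, later caregiver QoL) the main mediation analysis.
2. Adjust it for both members' baseline QoL, diagnosis, and shared-cause covariates already collected. Fix these in advance because they may affect both members' QoL, whether or not they differ between arms. Household composition, relationship to the veteran and veteran comorbidity are candidates.
3. Add a sensitivity analysis showing how strong a residual mediator–outcome correlation would have to be to explain the indirect effect. This is essential, because neither lagging nor baseline adjustment removes the bias.
4. Report the concurrent model as association between dyad members.
5. Align the wording that claims to determine the mediated amount with the exploratory wording of the dyad paragraph, and apply the same rules to the burden, depression and anxiety mediation models.

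The cost is SAP wording and modest programming on data already collected. The price is a wider interval, a weaker claim and the possible loss of a truly concurrent effect.

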#### QoL

The primary outcome is QoL (Quality of Life in Alzheimer’s Disease scale [QOL-AD]) measured with a 13-item scale [39, 40] designed to provide both a patient report and a caregiver report of QoL [39, 40]. Responses are structured in a four-choice format (i.e., poor, fair, good, or excellent) that is consistent across all questions, and all items are rated according to the caregiver’s or veteran’s current QoL. The scale includes appraisal of physical QoL, mood, interpersonal relationships, ability to participate in meaningful activities, financial situation, and overall assessment of QoL. Psychometric properties indicated that the QOL-AD has both content validity and criterion content validity when correlated with the Dementia Quality of Life Instrument (*r* = 0.69) and the EuroQol EQ-5D scale (*r* = 0.54). While QOL-AD has good construct validity, both interrater reliability (Cohen’s kappa > 0.70) and internal consistency (Cronbach’s alpha coefficient = 0.82) were excellent [41]. In a more recent evaluation, the QOL-AD demonstrated acceptable reproducibility at 2 weeks with intraclass correlation coefficient (ICC) > 0.80 and internal consistency with Cronbach’s alpha coefficient > 0.70. In fact, Wolak-Thierry et al. [42] reported that the QOL-AD was preferred over the general health dimension of the Duke Health Profile because the QOL-AD was significantly (*P* < 0.0001) more efficient in time required to complete [41, 42].

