#### Depressive and anxiety symptoms

We use the 10-item Center for Epidemiologic Studies Depression Scale (CES-D) [53–55] to determine the impact of the ABC ANSWERS intervention on caregivers’ and veterans’ depression. The CES-D is a 10-item depression scale with a total score ranging from 0 to 30, with higher scores indicating more symptoms of depression and a score ≥ 10 indicating depression [55]. To measure anxiety symptoms, we use the Generalized Anxiety Disorder 7-item scale (GAD-7), which is a 7-item anxiety scale with a total score ranging from 0 to 21 [56]. Both the CES-D and the GAD-7 have good internal consistency and test–retest reliability, as well as convergent, construct, criterion, procedural, and factorial validity for the diagnosis of major depression and general anxiety disorder [56–58]. We have used both instruments in multiple research studies, including our dementia collaborative care trials [2, 4, 10, 25–28, 30, 31, 56, 57].

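### The exploratory dyad analysis labels the veteran–caregiver ICC as agreement, although for CES-D, GAD-7 and QoL each member is scored on his or her own state

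*Protocol article*

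**What the plan says.** The dyad paragraph of the Analysis plan (Protocol article) opens with an aim of association: to "assess how caregivers’ outcomes are related to veterans’ measures". It then moves to agreement. The next sentence reads "We will first explore the degree of concordance between paired veteran–caregiver reports", and the one after gives the purpose of the ICCs as to "assess the degree of chance-corrected agreement between individual veteran and caregiver outcomes", controlling for within-person correlation over time.

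Other sections say who is being scored:

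- **Depression and anxiety.** Under Depressive and anxiety symptoms, the CES-D is used "to determine the impact of the ABC ANSWERS intervention on caregivers’ and veterans’ depression". The Analysis plan places CES-D, GAD-7 and dyadic strain among "outcomes collected on both veteran and caregiver", with separate models for veterans and caregivers.
- **QoL.** The QoL section describes the QOL-AD as "designed to provide both a patient report and a caregiver report of QoL", and then says that "all items are rated according to the caregiver’s or veteran’s current QoL". The Background and the outcomes section list caregiver QoL and veteran QoL as separate outcomes.

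**The concern.** Agreement and concordance describe how closely two raters score one target. A veteran's depression score and a caregiver's depression score have two targets. The veteran has dementia or a brain injury and the caregiver in general does not, so a difference in average level between them would be no surprise. An agreement coefficient counts that difference as error.

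At stake is a wrong exploratory conclusion. A low ICC could be reported as poor concordance between veteran and caregiver reports when it shows only that two people differ in level. It would also fail to answer the paragraph's own opening question, which is about relationship.

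**Working it through.** The article gives no ICC value, target or precision, so there is no figure to reproduce. The check has two parts.

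**1. Who is rated, outcome by outcome**

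| Outcome | What the article says is scored | Is agreement meaningful? |
|---|---|---|
| CES-D | Each member's own depression | No |
| GAD-7 | Each member's own anxiety; collected on both | No |
| QOL-AD | The caregiver's or the veteran's current QoL; two separate outcomes | No, if each rates his or her own QoL, which is how the sections read together |
| Dyadic relationship strain | A relationship that both members share | Possibly |

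**2. What the agreement form does to the number (illustration)**

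Inputs, all assumed because the article gives none: both members' scores have variance 1, the within-dyad correlation is r, and the members' means differ by d SD.

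- The variance between dyads is r and the residual variance is 1 − r.
- Two role means that are d apart have variance d²/2.
- Consistency ICC = r / (r + 1 − r) = r, whatever d is.
- Absolute-agreement ICC = r / (r + 1 − r + d²/2) = r / (1 + d²/2).

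| r | d = 0 | d = 0.5 (divide by 1.125) | d = 1 (divide by 1.5) |
|---|---|---|---|
| 0.30 | 0.30 | 0.27 | 0.20 |
| 0.50 | 0.50 | 0.44 | 0.33 |
| 0.60 | 0.60 | 0.53 | 0.40 |

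At d = 1 the agreement form loses one third of its value for every r, although the link between the members is unchanged.

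**Precision of the alternative.** With the 180 dyads that the Statistical power section expects to remain, Fisher's z has standard error 1/√177. For r = 0.30 the 95% CI is tanh(atanh 0.30 ± 1.96/√177), or about 0.16 to 0.43. The correlation at a visit can therefore be estimated usefully from the data already planned.

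**The case against.** The strongest reply is that the statistic is sound and only its label is off. An ICC between dyad members is a standard index of interdependence and serves the aim in the paragraph's first sentence. With equal variances, a consistency ICC equals the correlation recommended here. The article does not name the ICC form, a detail that a condensed article may leave to the full plan. If that form is consistency, or the model has a fixed effect for member role, the mean-gap penalty is zero. All of this stands. It rules out the stronger inference that the ICC answers no valid question. What remains is that the article does state a purpose, chance-corrected agreement, and that purpose is wrong for these outcomes.

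A second reply is that agreement is not always misplaced. Dyadic relationship strain is collected on both members and may concern one shared relationship, so concordance is a fair question there. This also stands, and the fix keeps it.

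A reader might also infer that the agreement wording blurs whose QoL is the primary outcome, because the phrase about a patient report and a caregiver report could mean self and proxy ratings of the veteran. The documents do not support this. That phrase describes what the scale was designed to provide. The sentence on how items are rated refers to the caregiver's or the veteran's current QoL. The two are listed as separate outcomes and modelled separately, and veteran QoL is examined as a mediator of caregiver QoL. The Statistical power section does name veteran QoL as primary, against the outcomes section, but that is a separate inconsistency which the ICC neither causes nor affects.

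**Conclusion.** The point holds as a minor correction to an exploratory analysis. For CES-D, GAD-7 and QoL, agreement is the wrong estimand, because each member is scored on his or her own state and the stated aim is to relate the two members' outcomes.

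The size is conditional. If an absolute-agreement ICC were used, a 1 SD mean gap would reduce 0.60 to 0.40 and a 0.5 SD gap would reduce it to 0.53. With no gap, or with a consistency ICC, nothing is lost. These figures assume equal variances; the correlation and the gaps are illustrative and do not come from the article. For QOL-AD the conclusion also rests on the reading that each member rates his or her own QoL, which the sections taken together support.

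The ICC does not enter the treatment comparisons, the power calculation or the type I error, and it has no bearing on which outcome is primary.

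**What to change.** In the dyad paragraph of the Analysis plan:

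- For CES-D, GAD-7 and QoL, replace the agreement ICC with the within-dyad correlation at each visit, with a 95% CI, from a bivariate mixed model of veteran and caregiver scores. A consistency ICC from a model with a fixed effect for member role would also do.
- Describe the result as interdependence between members.
- Keep the words agreement and concordance only where both members rate the same target, such as their shared relationship strain.

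The cost is a few sentences and a different model statement. The data and the sample size are unchanged.

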#### Statistical power

Power estimation was conducted using the GLMPOWER procedure in SAS 9.4 software, which takes into account the repeated measures. Power was estimated under two scenarios for potential intervention effects for the primary outcome of veteran QoL. In the first scenario, we assume an early intervention effect with a 0.3 standard deviation (SD) effect size at 3 months and sustained intervention effects of 0.3 SD at 6 and 12 months. In the second scenario, we assume that the effect of intervention is gradual in a dose–response fashion (i.e., 0.17 SD, 0.34 SD, and 0.68 SD effect sizes at 3, 6, and 12 months, respectively). We further assumed a Toeplitz pattern for the correlation structure with correlations of 0.4 for adjacent measures and 0.2 for measures farther apart. With the total enrollment of 200 veteran–caregiver dyads, we expect 10% loss to follow-up rate due to refusal or death. With 180 veteran–caregiver dyads remaining, both scenarios will have > 80% power to detect an intervention effect from a linear mixed model with type I error set at 0.05. Power will be similar for other aims.

